### Five-week intervention period starting at birth

The mother will be asked to inform the researcher of the baby’s birth by e-mail, text message or telephone. Five days after birth, the researcher will telephone all mothers to assess the eligibility criterion of the baby and to remind them to fill out the daily contact logbook and the weekly feeding and sleep logbook. Also, the researcher will ask if they have any questions or comments. If the mother is in the SSC condition, the researcher will encourage her to provide daily SSC to the infant.

### Assessment on week two after birth

Thirteen days after birth, all mothers will receive an e-mail or text message to remind them to fill out the additional questionnaires, the 72-h infant crying and sleep logbook, the maternal sleep logbook, and to collect an infant stool sample the next day. Fifteen days after birth, all mothers will be telephoned to ask for questions or comments related to the data-collection on week 2. Also, the home visit on week 5 will be arranged, preferably 4 days after the infant becomes 5 weeks of age.

### Week three and week four after birth

Twenty-one days and 28 days after birth an e-mail or text message will be sent to the mother to remind her to fill out the daily contact logbook, the weekly feeding and sleep logbooks, and she will be asked for any questions or comments. The mothers in the SSC condition will be encouraged to provide daily SSC to the infant.

### Home visit on week five after birth

On 34 days after birth, the experimenter will remind the mother to fill out the additional questionnaires, the 72-h infant crying and sleep logbook, the maternal sleep logbook, and to collect an infant stool sample on week 5. One day before the expected home visit an e-mail or text message will be sent to the mother to reconfirm the home visit. During the home visit, the mother will bathe her infant as usual. Saliva will be collected from both the mother and infant before and two times (25 and 40 min) after the bathing session. The bathing session will be videotaped to observe the quality of maternal caregiving behavior from tape. Also, the researcher will copy the logbook of the maternity carer from the first week after birth. In addition, a hair sample will be collected from the mother for the assessment of maternal physiological stress levels. The experimenter will collect all study questionnaires, logbooks and samples to take back to the lab.

### Assessment on week twelve after birth

Between week 5 and week 12, the mother will be reminded on week 7 and week 9 to fill out the short weekly questionnaire on infant contact, feeding, and sleep by e-mail or text-message. On week 12, the experimenter will send an e-mail to the mothers to remind her to fill out the digital version of the additional questionnaires and to fill out the 72-h infant crying and sleep logbook and the maternal sleep logbook. Afterwards, the mothers will send the logbooks and a copy of the growth curve of the well-baby clinic by post.

### Follow-up assessment on one year after birth

One week before the child’s first birthday, all mothers will be telephoned to explain the study procedure on 1 year after birth and the experimenter will send a birthday card and information related to the stool sample to the mother. Also, a digital version of the additional questionnaires will be sent to the mothers by e-mail. Afterwards, the experimenter will visit the home to collect a stool sample and copy the infant’s growth curve from the well-baby clinic logbook. During this short visit, the mother will also receive the debriefing of the study.

### Data storage

All information will be stored with ID code numbers to maintain participant confidentiality. The ID code numbers will be unrelated to participants’ identifiers, except in a central file with the participants’ contact details. All records that contain names or other personal identifiers, such as informed consent forms, will be stored separately from study records identified by the ID code number. All study-related information on paper, including logbooks, questionnaires, and administrative forms, and the maternal hair samples will be securely stored in locked file cabinets in areas with limited access. Biological specimens, including maternal and infant saliva samples and infant stool samples, will be stored in medical refrigerators in the laboratory area, with limited access, of the Behavioural Science Institute. Digital and online information will be secured with password-protected access systems. Two investigators will check the imported data values before the data analyses. Only the principal investigators will be given full access to the data. The Behavioural Science Institute is currently working on an open access database. The entire dataset of this study will be included in this database after publication of all study reports. The dataset will only be shared without participant identifiers.

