### Objectives

The primary goal of this RCT, with two parallel groups (intervention versus passive control group), is to examine if daily mother-infant SSC is effective in decreasing (sub)clinical levels of maternal depressive symptoms in a non-clinical sample with full-term infants in comparison to mothers who care for their infant as usual. The intervention starts immediately after delivery and has a duration of 5 weeks. The secondary aim is to investigate additional maternal and full-term infant outcomes, and two possible underlying mechanisms: maternal oxytocin concentrations and infant intestinal microbiota. We hypothesize that, compared to the control (care-as-usual) group, the SSC group will show:

*Improved maternal outcomes:*

1. Mental health:lower levels of depressive symptoms (primary outcome);lower levels of anxiety;lower levels of stress;lower levels of traumatic stress following child birth;better sleep quality.

2. Physical health:better physical recovery from the delivery;better health (fewer illnesses and health problems);more frequent and a longer duration of breastfeeding;lower levels of physiological stress.

3. Mother-infant relationship:better bonding to the infant;better quality of maternal caregiving behavior.

*Improved infant outcomes:*

1. Behavior:lower amounts of daily fussing and crying;better sleep quality.

2. Physical health:better growth and health (fewer illnesses and health problems);lower levels of physiological stress.

3. General development:better regulation capacities;better social-emotional capacities;better language, cognitive, and motor capacities.

*Potential underlying mechanisms:*
higher levels of maternal oxytocin concentrations. Maternal oxytocin concentrations will mediate the relationship between SSC and maternal outcomes.more optimal levels of intestinal microbiota (i.e. faster developing microbiota, more diverse and more stable microbiota, and fewer potentially pathogenic bacteria). Infant intestinal microbiota will mediate the relationship between SSC and infant outcomes.

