## Methods

### Study design

This SSC intervention project in mothers and their full-term infants is a RCT with two parallel groups (intervention versus passive control group). The study has been designed in accordance with the SPIRIT 2013 statement (see Additional file 1 for complete checklist) [45]. Administrative information related to the trial can be obtained in Additional file 2. The project will start in April 2016. The expected total duration of the study from the start of recruitment to the last participant finishing the 1-year assessment is 20 months. The study will start with baseline measures in the last trimester of pregnancy. The intervention period will start immediately after birth and will have a duration of 5 weeks. Maternal and infant outcomes will be measured at 2 weeks, 5 weeks, 12 weeks and 1 year after birth.

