2.3 Breastfeeding	x(w1–12)			x	Weekly logbook	The mother will fill out a weekly logbook including the estimated times of breastfeeding, expressed breastmilk feeding, and formula feeding to examine breastmilk initiation, exclusivity, frequency and duration. At one year of age, mothers will note the number of months the infant was breastfed and she will note the current feeding status.
2.4 Physiological stress		x			Hair cortisol	Hair analyses will be used to show the activity of the HPA axis over longer periods of time. A strand of hair will be cut from the scalp.
3. Mother-infant relationship						
3.1 Mother-infant bond	x	x	x	x	Maternal Postnatal Attachment Scale (MPAS)	The MPAS is a 19-item validated questionnaire to assess current maternal attitudes, thoughts, and feelings towards the child [62].
3.2 Quality of maternal caregiving behavior (sensitivity)		x			Ainsworth Sensitivity Scales	An infant bathing session during the home visit on week five will be videotaped. After, reliable observers, blinded for group allocation, will observe maternal sensitivity [63].
3.3 Quality of maternal caregiving behavior (synchrony)		x			Saliva cortisol	Synchrony will be measured with saliva samples of both the mother and infant before and after the bathing session (undressing, bathing and dressing). Samples will be collected right before undressing (baseline, T1), and 25 (stress, T2) and 40 (recovery, T3) minutes after the infant is taken out of bath [64]. Saliva will be collected in tubes for the mother and with eye sponges for the child [65]. Cortisol synchrony consists of the within mother-infant dyad cortisol associations (i.e. mother cortisol predicting infant cortisol, infant cortisol predicting mother cortisol). Cortisol synchrony will be examined for every saliva sample (pre-stress, peak-stress, recovery), for total stress cortisol concentrations (Area Under the Curve (AUC)), and cortisol recovery (recovery – pre-stress).
Secondary outcomes: Underlying mechanism						
Oxytocin concentrations		x			Saliva oxytocin	Maternal oxytocin concentrations during the bathing session will be measured in saliva at the same time points as cortisol. Saliva will be collected in tubes.

**Table 2 Tab2:** Infant outcome measures

Construct	Timing (W = week/Y = Year)				Measure	Additional information
	W2	W5	W12	Y1		
Secondary outcomes						
1. Behavior						

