1.1 Crying and fussing	x	x	x		72-h study diary	Crying and fussing will be collected with a simply designed 72-h logbook that mothers fill in with lines [66].
1.2 Sleep quality	x	x	x	x	72-h study diary & Adjusted version Brief Infant Sleep Questionnaire (BISQ)	Mother will note the amount of sleep time in the crying and fussing diary at week two, week five, and week twelve [66]. Additionally, the mothers will complete the infant sleep-screening tool in reference to their child’s sleep during the past week at week two, week five, week twelve and year one [67].
2. Physical health						
2.1 Growth & health		x	x	x	Well-baby clinic logbook & Health interview and questionnaires	Growth and weight information will be copied from the well-baby clinic logbook at week 12 and year one. In addition, a health interview will be performed during the second home visit [61]. Also, the mother will fill in health questionnaires, based on the infant health interview, at week 12 and at 1 year of age [61].
2.2 Physiological stress		x			Saliva cortisol	Infant cortisol reactivity and recovery will be measured with the saliva samples of the infant during the bathing session [64].
3. General development						
3.1 Regulation capacities			x	x	Infant Behaviour Questionnaire Revised (IBQ) – Short form	The IBQ is a 91-item questionnaire to assess infant regulation capacities with the Orienting/Regulation subscale [68].
3.2 Language, cognitive and motor capacities				x	Ages and Stages Questionnaire- Third edition (ASQ-3)	The ASQ-3 is a 30-item validated questionnaire to assess communication, gross motor, fine motor, and adaptive problem solving skills [69]. The Personal-Social subscale of the ASQ will be used as a measure for social-emotional capacities (see 3.3).
3.3 Social-Emotional capacities				x	Brief Infant Toddler Social Emotional Assessment (BITSEA)	The BITSEA is a 42-item validated questionnaire to examine social and emotional behavior such as externalizing and internalizing behavior [70]. The Personal-Social subscale of the ASQ will be used (see 3.2) [69].
Secondary outcomes-Underlying mechanism						
Intestinal microbiota	x	x		x	Stool samples	Stool will be collected from the diaper by the parents. Stool will be collected in tubes.

**Table 3 Tab3:** Additional information

Measure	Timing (P = late pregnancy/W = week/Y = Year)					Details
	P	W2	W5	W12	Y1	
Eligibility criteria						

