### Recruitment

The recruitment includes a cover story. Mothers will be told that the study will focus on the relationships between infant sleep and feeding behavior, mother-infant contact, and maternal and infant mental and physical health. In addition, the mothers will be told that a subgroup of the pregnant women will be asked to implement a natural and simple 5-week daily contact period with their newborn infant, starting immediately after birth.

Women will be recruited from a database of pregnant women who have expressed their interest for participating in scientific research. In addition, the experimenter will recruit women at pregnancy clubs, baby fairs, and baby shops. All expectant women will be informed about the study with the study flyer and study website.

After signing up, all expectant mothers will be telephoned by the principle investigator to provide more information about the study. The eligibility questionnaire will assess the eligibility of the mother. Next, a home visit in late pregnancy (week 34–36) will be arranged for interested and eligible women to explain the study in person by the principle investigator.

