### Dissemination

Data will be analysed when all the data is collected. The principal investigators will make every attempt to reduce the interval between the completion of data collection and the release of study results to a minimum. The principle investigators will justify names for authorship regarding topics suggested for presentation or publication. Data will only be reported study-wide. The study results will be released in a study-wide manner to participants after publication of the results. Also, the study results will be released to the general public by several channels, including international high impact journals and, at a national level, by oral presentations in health care organizations to inform nurses, midwifes, pediatricians and mental healthcare practitioners about this intervention method.

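### Saliva and stool are assigned to refrigerators, with no freezing step or holding limit stated, which can add storage-related error to both planned mediators and to the salivary cortisol outcomes

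*Protocol article*

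**What the plan says.** The Data storage section names one storage condition for saliva and stool: "Biological specimens, including maternal and infant saliva samples and infant stool samples, will be stored in medical refrigerators in the laboratory area". The same section sends maternal hair to locked file cabinets, so storage was distinguished by specimen type. Freezing, a preservative, a temperature, a holding limit and an assay date appear nowhere in the article.

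The specimens concerned are:

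- **Saliva**, taken at week 5 only: "Saliva will be collected from both the mother and infant before and two times (25 and 40 min) after the bathing session". It carries infant cortisol, mother-infant cortisol synchrony and the first mediator: "Maternal oxytocin concentrations during the bathing session will be measured in saliva at the same time points as cortisol".
- **Stool**, marked in Table 2 at week 2, week 5 and 1 year: "Stool will be collected from the diaper by the parents. Stool will be collected in tubes". It carries the second mediator.

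The Objectives section hypothesises, for the intervention arm, "faster developing microbiota, more diverse and more stable microbiota, and fewer potentially pathogenic bacteria". The Data-analysis section enters oxytocin and microbiota as mediators in structural equation models.

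On timing, the Study design section says: "The expected total duration of the study from the start of recruitment to the last participant finishing the 1-year assessment is 20 months". The Dissemination section says: "Data will be analysed when all the data is collected".

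**The concern.** The article states a storage condition here, and staff who followed the text would leave a peptide hormone in saliva, and stool with no stated preservative, unfrozen. It is general laboratory knowledge, taken here as an assumption because the documents contain no stability data, that refrigeration slows enzymatic breakdown and bacterial growth but does not stop them. The values read at assay would then partly reflect how long and how cold a sample was kept.

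Error of this kind in a mediator weakens the standardised difference between arms and the estimated indirect effect. A null mediation result would be harder to interpret. For microbiota, selective growth could also alter the diversity index and the count of potentially pathogenic bacteria. Faster development and greater stability are judged by comparing stools from the same infant at different ages, and those stools may have been stored for very different times. The samples cannot be retaken: saliva is collected at one visit, and an infant passes week 2 and week 5 once.

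**Working it through.** No figure in the plan needs reproducing. The check is calendar arithmetic on holding time, under the assumption of **one batch assay at month 20**. The article does not state this.

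**Inputs**

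- Study length T = 20 months (Study design).
- Enrolment at gestational week g = 34 to 36: "a home visit in late pregnancy (week 34–36) will be arranged for interested and eligible women" (Recruitment). The first such visit is taken as month 0. If recruitment began earlier, the first participant's times below are slightly too long.
- Birth at gestational week b. The floor of 37 is an eligibility criterion (Participants). The values 40 and 42 are assumptions.
- Sampling at s = 2 or 5 weeks, or 12 months, after birth (Tables 1 and 2).
- Weeks per month: 52.1775 / 12 = 4.348.

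**First participant.** Holding time = 20 − (b − g)/4.348 − s/4.348 for weeks 2 and 5, and 20 − (b − g)/4.348 − 12 for the 1-year stool.

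| g, b | Enrolment to birth (months) | Week-2 stool | Week-5 saliva and stool | 1-year stool |
|---|---|---|---|---|
| 36, 37 | 0.23 | 19.3 | 18.6 | 7.8 |
| 35, 40 | 1.15 | 18.4 | 17.7 | 6.9 |
| 34, 42 | 1.84 | 17.7 | 17.0 | 6.2 |

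Middle row, week 2: 20 − 1.15 − 0.46 = 18.4 months.

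**Last participant.** Her 1-year visit ends the study, so holding time = 12 − s/4.348.

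- Week-2 stool: 12 − 0.46 = 11.5 months.
- Week-5 samples: 12 − 1.15 = 10.9 months.
- 1-year stool: about 0 months.

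The early samples would therefore be held about 11 to 19 months, and none for the full 20.

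**Within one infant.** Whatever the enrolment date, the week-2 stool would be held 12 − 0.46 = 11.5 months longer than the same infant's 1-year stool. Storage time and infant age would be tied together for every infant.

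**Before the laboratory.** The week-2 section has the stool collected the day after the day-13 reminder, that is on day 14. The week-5 visit is preferably 4 days after the infant reaches 5 weeks: 35 + 4 = day 39. The week-5 section has the experimenter take the samples to the laboratory then, and no earlier pick-up is described. On that reading the week-2 stool stays at home for 39 − 14 = 25 days, under conditions the article does not state.

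**If assays are run on a rolling basis**, laboratory holding could be days or weeks. The documents do not decide between the two cases.

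**The case against.** The strongest reply is that the Data storage section is about confidentiality and access, so its reference to refrigerators says where specimens are secured and is not a laboratory specification. The term may loosely cover freezers, and a condensed article commonly leaves temperatures and assay timing to a laboratory manual. It stands that the wording may be loose and that the missing temperature alone would be no finding. But the article does name a condition, for these specimens specifically, and nothing elsewhere corrects it.

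Four stronger readings are tempting, and the documents do not support them:

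- **That assay waits until all data are in.** The Dissemination sentence concerns data analysis. Assay results may be among the data already collected by then.
- **That samples are stored for 20 months.** That figure is the length of the study.
- **That the mediators may go unmeasured.** The most that follows is added error in the measured values.
- **That a loss of power can be quoted for this trial.** Any such figure needs an assumed effect and an assumed reliability. The documents tie neither to storage, and the 84 dyads were sized for depressive symptoms.

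It also stands that storage is the same in both arms. Stratified 1:1 randomisation in blocks of 4 and 6 keeps the arms close to balanced over enrolment order, so variation in storage time should not systematically favour one arm. The confounding of storage time with age is likewise shared by the arms. It distorts the developmental trend and adds noise to the arm comparison.

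**Conclusion.** The point holds in limited form. Refrigerators are the only storage the article names for saliva and stool, and no freezing step, preservative or holding limit is stated. Taken literally, this can add storage-related error to both mediators and to the salivary cortisol outcomes. The expected effect is mainly noise and attenuation in secondary mechanism analyses. Its size is unknown, because the documents give no degradation rate.

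The range of about 11 to 19 months for early samples, and the resulting confounding with infant age, depend on an end-of-study assay and on birth at 37 to 42 weeks. With rolling assay, laboratory holding could be far shorter.

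The primary outcome is a questionnaire, so it and the sample size are untouched. Maternal hair cortisol is stored separately and is not part of this point. The change is still worth making, because the samples cannot be collected again.

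**What to change.** In Data storage, replace the refrigerator wording with frozen storage for saliva and stool, from as soon as possible after collection until assay. The assay laboratory should set the temperature and the maximum holding time.

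Freezing only on arrival at the laboratory would not be enough. The text must also cover the week-2 stool between collection and the week-5 visit, for example by freezing at home or by earlier pick-up.

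Record the collection, freezing and assay dates for every sample. Assay each dyad's samples together, in batches balanced by arm. If freezers were meant all along, correcting the sentence and adding the home-storage step settles the matter.

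The cost is freezer space and minor logistics for the week-2 stool. No extra samples or participants are needed, and no extra visits unless early pick-up is chosen.

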### Data-analysis

Data will be handled according to standard procedures. Demographic characteristics and study outcomes will be described for each treatment group using means and standard deviations for continuous outcomes. Proportions for categorical data will be provided. The pattern of missingness will be checked before the analyses. All measures will be controlled for outliers and checked for normality. Skewed continuous outcomes will be transformed. The level of significance (*p* -value) is set at *p* < .05 in all analyses.

We will conduct intention-to-treat analyses, in which participants are compared according to the group they were randomly assigned to regardless of participants’ compliance, including SSC protocol adherence, or withdrawal from the study, and analyses on imputed datasets based on the multiple imputation method [52]. Primary and secondary outcomes, that will be examined once, will be compared within multivariate analyses of covariance. Multilevel mixed models will be used for repeated measures. Microbiota composition will be examined with the Pearson’s moving window correlation. Microbiota diversity will be calculated with the Simpson’s reciprocal index of diversity (1/D). The Benjamini and Hochberg method will analyse differences between the SSC group and the control group. The analyses will be adjusted for potential confounding factors identified a priori (see Table 3). Structural equation models will be used to examine the mediation effect of the potential underlying mechanisms, maternal oxytocin concentrations and infant intestinal microbiota, on maternal and infant outcomes, respectively.

